## Abstract

**Background:**

Foot orthoses are frequently used for the prevention of lower limb overuse injuries but evidence for their effectiveness is limited. The primary aim of this study is to determine if prefabricated foot orthoses reduce the incidence of lower limb overuse injuries in naval recruits undertaking 11 weeks of basic training.

**Methods:**

This study is a participant and assessor blinded, parallel-group, randomised controlled trial. The trial will recruit participants undertaking 11 weeks of basic training at the Royal Australian Navy Recruit School, Cerberus, Victoria, Australia. Participants will be randomised to a control group (flat insole) or an intervention group (prefabricated foot orthosis). Over the 11 weeks of basic training, participants will document the presence and location of pain in weekly self-report diaries. The end-point for each participant will be the completion of 11 weeks of basic training. The primary outcome measure will be the combined incidence of four lower limb injuries (medial tibial stress syndrome, patellofemoral pain, Achilles tendinopathy, and plantar fasciitis/plantar heel pain) which are common among defence members. Secondary outcome measures include: (i) overall incidence of lower limb pain, (ii) severity of lower limb pain, (iii) time to injury, (iv) time to drop-out due to injury, (v) adverse events, (vi) number of lost training days, (vii) shoe comfort, and (viii) general health status. Data will be analysed using the intention-to-treat principle.

**Discussion:**

This randomised controlled trial will evaluate the effectiveness of prefabricated foot orthoses for the prevention of common lower limb overuse injuries in naval recruits.

**Trial registration:**

Australian New Zealand Clinical Trials Registry: ACTRN12615000024549.

## Background

Lower limb overuse injuries are common in people who participate in regular physical activity [1–4]. For example, the incidence of lower limb overuse injuries among long-distance runners and physically active defence members has been reported to range from 19 to 79 % [3, 4]. The most common injuries include medial tibial stress syndrome, patellofemoral pain, Achilles tendinopathy and plantar fasciitis/plantar heel pain [1–3]. Lower limb injuries result in lost training time, incur financial costs, adversely affect an individual’s physical and mental health, and increase the likelihood of stopping physical activity [5].

Given the high incidence and detrimental effects of lower limb overuse injuries, interventions that are effective at preventing injuries are likely to have a significant positive impact on health-related quality of life [5]. However, a recent systematic review concluded that there is only weak evidence to support the use of interventions, including foot orthoses, to prevent lower limb injuries and more high quality trials are needed [6].

Foot orthoses are commonly used [7], having been shown to be beneficial for treating several musculoskeletal disorders of the lower extremity [8–10], as well as reducing the incidence of shin splints [11] and femoral stress fractures [12]. Although the specific mechanism of action by which foot orthoses provide benefits remains unclear, there is evidence that they alter kinematics, kinetics, and/or muscle activity of the lower limb [13]. Evidence to support the use of foot orthoses to prevent lower limb injuries is limited, though, as existing trials are generally of poor methodological quality [9, 14].

Therefore, this study aims to determine if prefabricated foot orthoses reduce the incidence of common lower limb overuse injuries in naval recruits undertaking 11 weeks of basic training.

## Methods

### Design

The Australian Navy Cerberus Orthotic Research (ANCOR) study is a participant and assessor, parallel-group blinded, randomised controlled trial. Participants will be randomised to a control group (flat insole) or an intervention group (prefabricated foot orthoses). To ensure allocation concealment, permuted block randomisation with random block sizes, stratified by sex, will be undertaken using an interactive voice response telephone service provided by the NHMRC Clinical Trials Centre (University of Sydney, New South Wales, Australia). The end-point for each participant will be the completion of their 11 week basic training programme. The location of the trial will be at the Royal Australian Navy Recruit School, Her Majesty's Australian Ship (HMAS), Cerberus, Victoria, Australia (HMAS Cerberus). The trial has been registered on the Australian New Zealand Clinical Trials Registry (ACTRN12615000024549). The findings from the trial will be reported according to the Consolidated Standards of Reporting Trials (CONSORT) statement [15, 16].

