#### Session 1 (baseline)

An initial assessment will be performed to determine the eligibility of participants. Injury history, general demographic data, physical assessments and anthropometric measures will be collected. This will include participants’ age, sex, waist and hip circumference, height and weight, foot posture [27], ankle joint dorsiflexion [28, 29], and a rating of lumbopelvic stability [30]. General health status will be determined using the Short-Form-12 Version 2 questionnaire [31] and physical activity (domestic, travel, work and recreation) in the previous four weeks will be measured using the Recent Physical Activity Questionnaire (RPAQ) [32]. Participants will also undergo a brief physical examination to determine if the clinical features used for the diagnosis of the four most expected lower limb injuries (Table 1) are present. Fitness information (e.g. multistage 20 m shuttle run test results) collected by Defence during the initial weeks of basic training will also be obtained for each participant.

**Table 1 Tab1:** Clinical features used for the diagnosis of the four most expected lower limb injuries

Injury	Clinical features
Medial tibial stress syndrome	Diffuse pain or oedema along the posteromedial border of the tibia;
	Pain spread over a minimum of 5 cm;
	Pain occurs with activity and lasts for at least a few hours post activity;
	Diffuse discomfort produced with palpation along the posteromedial border of the tibia, with discomfort confined to this region; and
	No history of paraesthesia.
Patellofemoral pain	Insidious onset of peripatellar or retropatellar knee pain;
	Pain on patellofemoral joint compression or resisted isometric quadriceps contraction at 30 degrees of knee flexion; and
	Peripatellar or retropatellar knee pain being provoked by at least two of the following activities: running, hopping, walking, marching, squatting, stair negotiation, prolonged sitting, or kneeling.
Achilles tendinopathy (midportion)	Insidious onset of pain located within 2 to 7 cm proximal to the insertion on the calcaneus; and
	Pain is reproducible with palpation of the Achilles tendon within 2 to 7 cm proximal to the insertion on the calcaneus; and
	Pain most noticeable after an extended period of rest and aggravated with activity.
Plantar fasciitis/plantar heel pain	Presence of pain in the plantar heel or medial arch;
	Pain is worse after rest but eases with mild activity;

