### Statistical analysis

Statistical analysis will be performed using SPSS version 22.0 or later (SPSS Corp, Chicago, Ill, USA) using the intention-to-treat principle, where all randomised participants will be included in the final analyses. The endpoint will be the completion of the 11 weeks of basic training for each participant. Multiple imputation will be used to replace any missing data using five iterations, with age, and group allocation as predictors [43]. The exception will be for the variable adverse events where no data substitution will be applied.

Participant characteristics and baseline data will be summarised by descriptive statistics. Distribution of continuous variables will be checked for normality and transformation will be carried out if necessary prior to the use of parametric statistics. Outcome data will be analysed according to a pre-planned protocol. Differences in the primary and secondary outcome measures between the two groups will be compared.

The differences between groups for the primary outcome measure of the combined incidence of the four common lower limb injuries (medial tibial stress syndrome, patellofemoral pain, Achilles tendinopathy, and plantar fasciitis/plantar heel pain) and the secondary outcome measure of the incidence of lower limb pain (overall and body region specific) during the 11 week training period will be compared using incidence rate ratios.

In regard to the other secondary outcomes, differences between groups for continuous outcome measures (severity of pain, lost training days and shoe comfort) will be analysed using independent t-tests. The time to lower limb injury and pain and drop-out will be compared using Cox proportional hazards ratios. Adherence of the shoe insole interventions will also be analysed using independent *t*-tests. The difference between groups for the outcome measure of health status (SF-12) will be compared using analysis of covariance (ANCOVA) with baseline scores and intervention group entered as independent variables [44].

95 % confidence intervals will also be provided to indicate precision of point estimates. We will also conduct hypothesis tests where appropriate, which will be considered significant if *p* < 0.05. Effect sizes will be determined using standardised mean differences (Cohen’s *d*) for continuous data.

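### Randomisation is stratified by sex, but no stated analysis uses sex; if sex predicts the outcome, the comparisons are slightly conservative

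*Protocol article*

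**What the plan says.** The Design section states that "permuted block randomisation with random block sizes, stratified by sex, will be undertaken". No other stratification factor is given. The Session 1 (baseline) section lists sex among the recorded characteristics, so the variable is available for every participant.

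The Statistical analysis section announces that "Differences in the primary and secondary outcome measures between the two groups will be compared" and then gives the methods:

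- **Primary outcome and incidence of pain:** incidence "during the 11 week training period will be compared using incidence rate ratios". No covariate or stratum is named.
- **Continuous secondary outcomes:** "severity of pain, lost training days and shoe comfort) will be analysed using independent t-tests". Adherence is also compared by t-test.
- **Times to event:** "The time to lower limb injury and pain and drop-out will be compared using Cox proportional hazards ratios". No covariate or stratum is named.
- **SF-12:** "analysis of covariance (ANCOVA) with baseline scores and intervention group entered as independent variables". The terms are listed, and sex is not among them.
- **Missing data:** "Multiple imputation will be used to replace any missing data using five iterations, with age, and group allocation as predictors". Sex is absent here too.

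**The concern.** Permuted blocks within sex keep the two arms close to equal in their proportion of women. If sex predicts the outcome, this balance removes the part of the chance variation between arms that comes from sex. An analysis without sex still counts that part in its standard error. It therefore reports more uncertainty than the design carries: confidence intervals are somewhat too wide, the real type I error rate falls below the nominal 5%, and power is a little lower than it could be.

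At stake is a small amount of precision that the sponsor has already obtained through the randomisation and would leave unused. Naming the stratification factor in the models beforehand also avoids a later choice between adjusted and unadjusted results.

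**Working it through.** **1. The plan's own sample size.** Inputs from the Sample size section: control risk 0.30, a 50% reduction (so 0.15), alpha 5% (taken as two-sided), power 80%, drop-out 20%. With pooled variance and no continuity correction:

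n = [1.960 × √(2 × 0.225 × 0.775) + 0.842 × √(0.30 × 0.70 + 0.15 × 0.85)]² / 0.15² = 120.5, so 121 per arm.

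121 / 0.80 = 151.25, so 152 per arm and 304 in total, against the stated 306. The figure reproduces. It makes no use of sex. With 153 per arm and 20% drop-out, about 122 per arm are evaluable, and power is 80.5%.

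**2. What is assumed.** The documents give no female share f and no female:male risk ratio k. I take f = 15-35% and k = 1.0-2.5, with k the same in both arms and sex balanced across arms. The primary comparison is treated as a risk ratio with binomial variance.

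**3. Excess standard error of the log risk ratio.** An arm with risk p contributes (1 − p)/p (times 1/n) to the variance. The part due to sex is the same in either arm:

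C = f(1 − f)(k − 1)² / (1 − f + fk)².

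- At 30% versus 15%, the total is 0.70/0.30 + 0.85/0.15 = 2.333 + 5.667 = 8, so the share due to sex is 2C/8 = C/4.
- At 30% in both arms, the total is 2 × 2.333 = 4.667, so the share is 2C/4.667 = 0.429C.

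The reported standard error exceeds the true one by the factor 1/√(1 − share).

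Example, f = 0.20 and k = 2: C = 0.16/1.44 = 0.1111. At 30% versus 15% the share is 0.0278 and the factor 1.014. At 30% in both arms the share is 0.0476 and the factor 1.025.

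**4. Power at 122 per arm (difference in risks), same example.** The within-sex variances are 0.8 × 0.25 × 0.75 + 0.2 × 0.5 × 0.5 = 0.200 (control) and 0.8 × 0.125 × 0.875 + 0.2 × 0.25 × 0.75 = 0.125 (intervention). The true standard error is √(0.325/122) = 0.0516.

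- Ignoring sex, the null standard error is √(0.34875/122) = 0.0535 and power is Φ[(0.15 − 1.96 × 0.0535)/0.0516] = 81.0%.
- Stratified by sex, the null standard error is √(0.3375/122) = 0.0526 and power is Φ[(0.15 − 1.96 × 0.0526)/0.0516] = 81.8%.

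**5. Results over f = 15-35%.** The last two columns are for a 5% two-sided test.

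| k | SE excess, 30% v 15% | SE excess, 30% in both arms | Real alpha, sex ignored | Power lost (points) |
|---|---|---|---|---|
| 1.0 | 0 | 0 | 0.050 | 0 |
| 1.5 | 0.3-0.5% | 0.6-0.9% | 0.048-0.049 | 0.2-0.3 |
| 2.0 | 1.2-1.6% | 2.1-2.8% | 0.044-0.045 | 0.8-1.0 |
| 2.5 | 2.5-2.9% | 4.4-5.2% | 0.039-0.041 | 1.5-1.8 |

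**6. Check by simulation (unadjusted versus Mantel-Haenszel risk ratio stratified by sex).** At f = 0.20 and k = 2, the type I error rate is 0.042 against 0.048 and power 80.1% against 81.2%. The mean standard errors at 30% versus 15% are 0.2616 and 0.2580, a ratio of 1.014, which agrees with step 3. At f = 0.30 and k = 2.5, power is 81.0% against 83.0%.

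**The case against.** The strongest reply has four parts.

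**The article does not call its main analysis unadjusted.** A reader might infer that the primary and Cox comparisons are declared to be unadjusted. They are not: no covariates are named either way, and an unseen SAP could add sex. This stands. What is fixed without sex is the t-tests, which cannot carry a stratum, and the listed SF-12 terms. For the primary and Cox comparisons the point is an improvement to be written down, not a stated error.

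**The loss is conditional.** A reader might infer that precision is certainly lost. The documents do not show that sex predicts these injuries, and at k = 1 the loss is zero. This stands, so the range has to start at zero.

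**The effect is small.** The 5% figure for the standard error needs 30% risk in both arms. At the design's own 30% versus 15%, the maximum is about 3%. This also stands, and the error is in the safe direction.

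**The standard-error argument does not carry directly to the Cox models.** Adjusting for a prognostic factor changes the target to a conditional hazard ratio and does not generally shrink its standard error. The gain there is in power.

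A tempting extension fails. In Session 1, "Participants will also undergo a brief physical examination to determine if the clinical features used for the diagnosis" of the four injuries is present, and a reader might want those features, or intake cohort, as covariates too. Neither was a stratification factor. The documents give no figure for how well the features predict later injury. Separating new from pre-existing injury depends on the outcome definition, not on covariate adjustment.

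None of this removes the mismatch between a randomisation stratified by sex and analyses that make no stated use of it.

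**Conclusion.** The point holds as a minor one. Over the assumed ranges for the share of women and the risk ratio, the primary-outcome standard error is 0 to about 3% too large under the planned effect (up to about 5% with equal 30% risks), and 0 to about 2 percentage points of power are forgone. The estimate is not biased, type I error is not inflated, and the sample size needs no revision. The stronger reading, that the planned tests are invalid or the trial materially underpowered for this reason, is not supported. The size for the secondary outcomes cannot be worked out from the documents. For SF-12 it depends on what sex adds beyond the baseline score.

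**What to change.** State in the SAP, before unblinding, that sex enters the between-group analyses:

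- **Primary outcome and incidence of pain:** a risk or rate ratio model with sex as covariate, or a Mantel-Haenszel estimate stratified by sex.
- **Pain severity, lost training days, shoe comfort and adherence:** linear models with group and sex in place of the t-tests.
- **SF-12:** add sex to baseline score and group.
- **Times to event:** Cox models stratified by or adjusted for sex, with the result described as a conditional hazard ratio.

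Report unadjusted estimates alongside. As a consequence, sex should join age and group in the imputation model, so that the data are not imputed without a variable that the analysis uses. Covariates for baseline injury features or intake cohort are not part of this change.

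The cost is wording only. Sex is already collected, and N = 306 stays.

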### Ethical approval

Ethical clearance for this project was provided by the Australian Defence Human Research Ethics Committee (protocol number: 764–14) and the La Trobe University Faculty Human Ethics Committee (protocol number: FHEC 14/250). All participants will provide written informed consent prior to recruitment. Ethical standards will adhere to the National Health and Medical Research Council National Statement [17] and the World Medical Association’s Declaration of Helsinki [18].

### Participants

Participants will be naval recruits from the Australian Defence Force (ADF). The minimum age of entry for naval recruits is 17 years, with the maximum age being generally three to six years before the compulsory retirement age of ADF members (60 years) [19]. Prior to undertaking basic training, naval recruits must pass a pre-entry medical and fitness test [19]. Fitness requirements include a minimum of 20 sit-ups and a multistage 20 m shuttle run test [20] score of 6.1. The multistage 20 m shuttle run test involves running between two points that are 20 m apart and doing so within a series of pre-recorded audible beeps, with time between beeps decreasing as the test proceeds [20]. Achieving a shuttle run score of 6.1 equates to 43 shuttles or a total of 860 m in 5 min and 15 s. In addition, female and male recruits are required to perform a minimum of 6 and 15 push-ups, respectively. The maximum allowable body mass index (BMI) is 32.9 kg/m^2^; and recruits with a BMI less than 18.5 kg/m^2^ may be deemed temporary unfit by medical staff, with this decision determined in consideration of the recruit’s general and medical fitness.

All naval recruits undertaking 11 weeks of basic training at HMAS Cerberus will be invited to participate in the trial. Consecutive cohorts of recruits will be invited to participate until the pre-specified sample size (see below) is achieved. Participants will be excluded if they use foot orthoses or have a lower limb injury (causing pain of least 30 mm on a 100 mm visual analogue scale when at worst [21, 22]) at the time of recruitment. All recruits will be provided information about the study at the commencement of their 11 week training programme. Recruits interested in participating in the study will be invited to attend an initial appointment within their first week of training (session 1). Figure 1 outlines the flow of participants through the trial.

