#### Session 3 (week 11)

An exit interview will be conducted with an assessor that is blinded to group allocation in the final week of training (week 11). This session will be used to collect self-report diaries and confirm their accuracy and completeness with participants. In addition, if lower limb pain is being experienced by the participants at this session, the assessor will attempt to determine the presence of medial tibial stress syndrome [23], patellofemoral pain [36], Achilles tendinopathy [37], and plantar fasciitis/plantar heel pain [21, 38]. Finally, injury data will be cross-checked against ADF medical records.

All participants will remain blinded to their group allocation and will have a similar experience at all sessions regarding time spent with assessors, advice provided, and data collected. That is, the only difference between the groups will be the type of shoe insole received.

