### Definition of injuries

For the purpose of this trial, an injury will be defined by the presence of pain that scores at least 30 mm on a 100 mm visual analogue scale when at its worst [21, 22]. Due to the lack of evidence regarding the diagnostic accuracy of the lower limb injuries of interest, the diagnosis of medial tibial stress syndrome [23], patellofemoral pain [36], Achilles tendinopathy [37], and plantar fasciitis/plantar heel pain [21] will be determined using a pragmatic approach via clinical assessments based on definitions described in previous studies (Table 1).

Over the 11 weeks of basic training, participants will document the presence and location of pain on pain drawings in their weekly self-report diaries. The pain drawings will identify the presence and location of pain in the body or feet, but they will not provide a specific diagnosis regarding the cause of pain. Once the self-report diaries have been submitted at the exit interview, the assessors will use a transparent overlay divided into multiple body areas to determine pain location.

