### Outcome measures

The *primary outcome measure* will be the combined incidence of the four common lower limb injuries (medial tibial stress syndrome, patellofemoral pain, Achilles tendinopathy, and plantar fasciitis/plantar heel pain) as determined at medical appointments and by assessors at the exit interview (week 11).

*Secondary outcomes* include:(i)the overall incidence of lower limb pain as determined by pain drawings in self-report diaries, measured at week 11;(ii)the severity (usual and worst) of over-use lower limb pain as determined by the 100 mm VAS in self-report diaries, measured at week 11;(iii)the time (in days) to lower limb injury and pain as determined by self-report diaries and navy medical records, measured at weeks 1 to 11;(iv)time to drop-out from injury (in days) as determined by navy administration records, measured at weeks 1 to 11;(v)the type, frequency and severity (mild, moderate or severe) of self-reported adverse events (such as new pains, shoe/insole discomfort and blisters) will be obtained from the self-report diaries, measured at weeks 1 to 11;(vi)lost training days as determined by navy administration and medical records, measured at weeks 1 to 11;(vii)shoe comfort will be measured using a 100 mm visual analogue scale, measured at baseline and week 11;(viii)general health status will be determined using the Short-Form-12 (SF-12) Version 2 questionnaire [31], measured at baseline and week 11.

Shoe comfort will be determined using a 100 mm visual analogue scale, which has been shown to have good reliability [39]. The left end of the scale (0 mm) is labelled “not comfortable at all” and the right end of the scale (100 mm) is labelled “most comfortable imaginable”. Participants will be instructed to place a mark on the scale that represents their perceived comfort rating. Similarly, pain will be determined using a 100 mm visual analogue scale. To indicate the range of pain to participants, the left end of the scale (0 mm) is labelled “no pain” and the right end of the scale (100 mm) is labelled “worst pain imaginable”. The VAS has been shown to be a valid [40] and reliable [39] measure of pain.

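### Recruits may enter with lower limb pain under 30 mm, yet any diary pain counts as incident, which dilutes the pain-incidence and time-to-pain outcomes

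*Protocol article*

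**What the plan says.** **Entry.** Under Participants, the only exclusions are use of foot orthoses and recruits who "have a lower limb injury (causing pain of least 30 mm on a 100 mm visual analogue scale when at worst" at recruitment. Pain below that level does not exclude.

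**Baseline.** Session 1 takes place within the first week of training. It covers eligibility and includes a "brief physical examination to determine if the clinical features used for the diagnosis of the four most expected lower limb injuries" are present. The article does not say what follows from a positive finding. The list of baseline measures contains no map of current pain by body region. The body and foot pain drawings belong to the diary, which is handed out after the insoles have been fitted.

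**Injury.** Under Definition of injuries, "an injury will be defined by the presence of pain that scores at least 30 mm on a 100 mm visual analogue scale". The rating that counts is the worst pain.

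**Primary outcome.** The four conditions combined, "as determined at medical appointments and by assessors at the exit interview (week 11"). Under Session 3, the assessor looks for the four conditions "if lower limb pain is being experienced by the participants at this session".

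**Secondary pain outcomes.** Outcome measures lists "the overall incidence of lower limb pain as determined by pain drawings in self-report diaries", and the time in days to lower limb injury and pain. Statistical analysis compares the incidence of lower limb pain, overall and by body region, over the 11 weeks by incidence rate ratios, and the times by Cox models.

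**The concern.** The trial asks whether an orthosis prevents complaints, so an incidence outcome should count complaints that begin after fitting. For the two pain outcomes the case rule is any pain shaded in a diary, while the entry rule lets in anyone whose worst pain is under 30 mm. A recruit with, say, 20 mm of knee pain at session 1 is eligible, shades the knee in week 1, and is at once an incident case and one of the first events in the time-to-pain model. The diary ratings look back over the previous week, so a first entry may also cover days before the insole was fitted.

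Such cases were present before treatment and arise in both arms. They carry no information on prevention. They move the rate ratio and the hazard ratio toward 1 and make a real effect on pain harder to see.

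**Working it through.** **1. The rules side by side**

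| Outcome | Threshold to enter | Threshold to be a case | Must it be new since baseline? |
|---|---|---|---|
| Four injuries (primary), time to injury | worst pain under 30 mm | worst pain at least 30 mm | not stated, but the thresholds meet |
| Lower limb pain, overall and by region | worst pain under 30 mm | any pain on the drawing | not stated |
| Time to pain | worst pain under 30 mm | any pain | not stated |

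In the first row nobody can enter while already meeting the injury definition. In the other two rows, pain above 0 and below 30 mm is both admissible at entry and sufficient to be a case.

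**2. The plan's own figure**

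The sample size concerns the primary outcome and is not in dispute. Inputs from Sample size: 30 % against 15 %, 80 % power, alpha 5 % (two-sided assumed), drop-out 20 %.

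n per group = [1.96 × √(2 × 0.225 × 0.775) + 0.842 × √(0.30 × 0.70 + 0.15 × 0.85)]² / 0.15² = 120.5, so 121.

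Allowing for drop-out: 121 / 0.80 = 151.25, so 152 per group and 304 in total, against 306 stated. The figure reproduces to within two participants.

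**3. Size of the dilution in the pain outcomes**

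The documents give neither the share with pain at entry nor the expected incidence of new pain, so these inputs are assumptions:

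- share with pain under 30 mm at entry: f, the same in both arms in expectation;
- each of these recruits reports that pain in a diary and is counted, whatever the insole;
- among the rest, new pain occurs in 60 % (control) and 45 % (orthosis), a true ratio of 0.75.

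Observed proportion = f + (1 − f) × p.

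| f | Control | Orthosis | Ratio |
|---|---|---|---|
| 0 | 0.60 | 0.45 | 0.75 |
| 5 % | 0.05 + 0.95 × 0.60 = 0.62 | 0.05 + 0.95 × 0.45 = 0.4775 | 0.77 |
| 10 % | 0.10 + 0.90 × 0.60 = 0.64 | 0.10 + 0.90 × 0.45 = 0.505 | 0.79 |
| 15 % | 0.15 + 0.85 × 0.60 = 0.66 | 0.15 + 0.85 × 0.45 = 0.5325 | 0.81 |
| 20 % | 0.20 + 0.80 × 0.60 = 0.68 | 0.20 + 0.80 × 0.45 = 0.56 | 0.82 |

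At f = 15 % the risk difference shrinks from 0.15 to 0.66 − 0.5325 = 0.1275. These are ratios of proportions. A rate ratio on person-time would take other values but move in the same direction.

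**4. Time to pain**

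Under the same inputs with f = 15 %, pain already present supplies 0.15 / 0.66 = 23 % of control events and 0.15 / 0.5325 = 28 % of orthosis events. If that pain is reported at the first opportunity, these events all fall at the start of follow-up, where the arms do not differ, and they pull the hazard ratio toward 1.

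**5. What remains for the primary outcome**

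The exit diagnosis is triggered by any lower limb pain. Neither Session 3 nor Table 1 repeats the 30 mm threshold, and neither refers back to the baseline examination. An assessor working from those two places alone could diagnose, at week 11, a condition whose features were recorded at session 1 and whose pain never reached 30 mm. The general definition of injury, which is stated for the whole trial, argues against that reading but is not tied to the exit diagnosis in so many words.

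**The case against.** A reader might infer that every incidence outcome is diluted, the primary included, and that the trial is therefore underpowered. The documents do not support this. Entry and injury use the same 30 mm worst-pain threshold. A milder complaint that worsens to 30 mm is a new injury by the protocol's own definition, and the insole could plausibly affect that worsening: the Background cites benefit of orthoses in treating musculoskeletal disorders. A power loss for the primary outcome would need a prevalence the documents do not give, and every such recruit would have to be certain to become a case in both arms.

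Nor do the documents show that recruits with diagnostic features are admitted without limit. That can happen only where worst pain is under 30 mm. Silence on the use of the baseline examination does not prove that it is ignored.

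It can also be said that incidence ordinarily means new occurrence, and that a condensed article may leave the counting rule to a fuller document or the procedures manual. This has some weight. However, the article does state the entry threshold, the source of the pain outcome and the method of comparison, and taken together as printed these let existing pain count as new. If a rule exists elsewhere, stating it settles the point.

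Finally, randomisation balances such cases in expectation. That is correct: the consequence is attenuation, not a false claim of benefit.

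**Conclusion.** The point holds for the secondary outcomes of lower limb pain incidence and time to pain. As written, pain under 30 mm that was present at entry is counted as a new case and an early event, and both comparisons are pulled toward no difference. With 60 % against 45 % new pain and 5 to 20 % of recruits in pain at entry, a ratio of 0.75 becomes 0.77 to 0.82 (0.81 at 15 %). All of these inputs are assumed, as is the certainty that entry pain is reported in a diary. The direction does not depend on the exact values.

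For the primary outcome and time to injury, the shared 30 mm threshold gives adequate protection. What is left is a gap in wording at the exit diagnosis, to which no size can be attached, and the sample size stands.

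**What to change.** 1. **Pain outcomes.** Define incident lower limb pain, and the event for time to pain, as pain in a body region that was free of pain at the pre-allocation session. Record pain location at that session.
2. **Where no baseline location exists.** Recruitment began on 28 January 2015, so some recruits may have none. For them, count diary worst pain reaching the 30 mm threshold used at entry. The first diary should not stand in for a baseline map, because it is completed after allocation and fitting. The article does not say whether diary worst pain is rated separately by site, so this fallback may apply only to lower limb pain overall.
3. **Primary outcome.** State that the 30 mm threshold applies to the exit diagnosis. Add a sensitivity analysis that does not count a condition whose Table 1 features were present at the baseline examination.
4. **Population.** Keep every randomised recruit, who stays at risk for the other regions and conditions. Report the unrestricted pain analysis as a sensitivity analysis. The restrictions by region and by baseline features use only pre-allocation data, so the randomised comparison is preserved.

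**Cost.** Wording in the outcome definitions and analysis plan, one pain location record at baseline, and somewhat fewer events. The examination for the four conditions is already carried out; a baseline map of pain by region is not listed and would be an addition.
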